# Ticagrelor and preconditioning in patients with stable coronary artery disease (TAPER-S): a randomized pilot clinical trial

**DOI:** 10.1186/s13063-020-4116-7

**Published:** 2020-02-17

**Keywords:** Angina, Ischemic preconditioning, Ticagrelor, Clopidogrel, Adenosine, Fractional flow reserve, Intracoronary electrocardiography, Microvascular function, Microvascular dysfunction, Microvascular resistance

## Abstract

**Background:**

Ticagrelor is a reversibly binding, direct-acting, oral, P_2_Y_12_ antagonist used for the prevention of atherothrombotic events in patients with coronary artery disease (CAD). Ticagrelor blocks adenosine reuptake through the inhibition of equilibrative nucleoside transporter 1 (ENT-1) on erythrocytes and platelets, thereby facilitating adenosine-induced physiological responses such as an increase in coronary blood flow velocity. Meanwhile, adenosine plays an important role in triggering ischemic preconditioning through the activation of the A1 receptor. Therefore, an increase in ticagrelor-enhanced adenosine bioavailability may confer beneficial effects through mechanisms related to preconditioning activation and improvement of coronary microvascular dysfunction.

**Methods:**

To determine whether ticagrelor can trigger ischemic preconditioning and influence microvascular function, we designed this prospective, open-label, pilot study that enrolled patients with stable multivessel CAD requiring staged, fractional flow reserve (FFR)-guided percutaneous coronary intervention (PCI). Participants will be randomized in 1:1 ratios either to ticagrelor (loading dose (LD) 180 mg, maintenance dose (MD) 90 mg bid) or to clopidogrel (LD 600 mg, MD 75 mg) from 3 to 1 days before the scheduled PCI. The PCI operators will be blinded to the randomization arm. The primary endpoint is the delta (difference) between ST segment elevations (in millimeters, mm) as assessed by intracoronary electrocardiogram (ECG) during the two-step sequential coronary balloon inflation in the culprit vessel. Secondary endpoints are 1) changes in coronary flow reserve (CFR), index of microvascular resistance (IMR), and FFR measured in the culprit vessel and reference vessel at the end of PCI, and 2) angina score during inflations. This study started in 2018 with the aim of enrolling 100 patients. Based on the rate of negative FFR up to 30% and a drop-out rate up to 10%, we expect to detect an absolute difference of 4 mm among the study arms in the mean change of ST elevation following repeated balloon inflations. All study procedures were reviewed and approved by the Ethical Committee of the Catholic University of Sacred Heart.

**Discussion:**

Ticagrelor might improve ischemia tolerance and microvascular function compared to clopidogrel, and these effects might translate to better long-term clinical outcomes.

**Trial registration:**

EudraCT No. 2016–004746-28. No. NCT02701140.

**Trial status:**

Information provided in this manuscript refers to the definitive version (n. 3.0) of the study protocol, dated 31 October 2017, and includes all protocol amendments. Recruitment started on 18 September 2018 and is currently ongoing. The enrollment is expected to be completed by the end of 2019.

## Background

### Rationale

Ticagrelor is a reversibly binding, direct-acting, oral P_2_Y_12_ antagonist used for the prevention of atherothrombotic events in patients with acute coronary syndrome (ACS) [1]. It does not belong to thienopyridines; it is a carbocyclic nucleoside, representing a “first-in-class” cyclopentyl-triazolo-pyrimidine. In two phase II studies, dyspnea was noted to occur as a side effect to ticagrelor in a dose-dependent fashion, and in the PLATO study, a 6% absolute excess of dyspnea was observed in ticagrelor-treated patients compared with patients treated with clopidogrel [1]. In the ONSET/OFFSET study, dyspnea was more commonly associated with ticagrelor therapy in comparison with clopidogrel and placebo in patients with stable coronary artery disease (38.6%, 9.3%, and 8.3%, respectively) but was not associated with any adverse change in cardiac or pulmonary function [2]. Similar results were later confirmed in the population of patients with ACS [3].

The mechanisms for this side effect are largely unknown, although early data indicate that ticagrelor blocks adenosine reuptake through inhibition of ENT-1 transporter by erythrocytes [4], and intravenous adenosine infusion can cause transient dyspnea in the absence of bronchoconstriction [5]. Another mechanism potentially increasing adenosine levels by ticagrelor is reflected in adenosine triphosphate (ATP) release from erythrocytes [6]. Moreover, the biochemical comparison between ticagrelor and adenosine suggests their molecular similarity. Adenosine is a well-known key endogenous molecule that regulates tissue functions by activating four G-protein–coupled adenosine receptors: A1, A2A, A2B, and A3. Adenosine accumulates in the extracellular space in response to metabolic stress and cell damage, and elevations of adenosine are commonly encountered in conditions such as ischemia, hypoxia, inflammation, and trauma. Adenosine confers protective effects on the cell due to its anti-inflammatory, cardioprotective, cerebroprotective, antisclerotic, and antifibrotic properties, as well as by platelet inhibition and vasodilation [7].

Because to these effects of ticagrelor on adenosine biochemistry, chronic adenosine overload induced by ticagrelor was hypothesized to possibly contribute to the vascular outcome benefit observed in the PLATO trial, in addition to the inhibitory effect it has shown on platelet activity via P_2_Y_12_ receptor inhibition. Very recently, ticagrelor has been shown to increase adenosine-induced physiological responses in healthy human subjects by shifting the dose-response curve for adenosine-induced coronary blood flow velocity (CBFV) to the left and increasing area under the curve of CBFV [8]. Moreover, among patients with non–ST-segment elevation ACS that were treated with percutaneous coronary intervention (PCI) and received a maintenance dose of ticagrelor, a greater CBFV was observed compared to patients that received prasugrel maintenance dose in response to increasing adenosine concentrations [9]. These effects seem consistent with pharmacologically observed blockade of adenosine reuptake, as one of the pleiotropic effects exerted by the ticagrelor. An increase in adenosine bioavailability, as potentiated by ticagrelor, could have beneficial effects by both increasing coronary perfusion and enhancing the function of the microcirculation.

#### Activation of preconditioning

Ischemic preconditioning, consisting in episodes of ischemia as short as 5 min, followed by reperfusion, has been showed to protect the heart from a subsequent longer coronary artery occlusion by markedly reducing the amount of necrosis. Adenosine plays a key role in triggering ischemic preconditioning. Indeed, the stimulation of A1 adenosine receptors triggers a complex pathway that includes the epsilon isoform of protein kinase C, the ATP-dependent potassium channels, and the mitochondrial permeability transition pores, as well as other cellular pathways, like a paradoxical protective release of oxygen radicals eventually making cardiomyocytes more resistant to ischemia [10, 11]. In humans, examples of preconditioning are the pre-infarction angina and the angina “warm-up” phenomenon. Preconditioning can be reproduced experimentally by repetitive and sequential balloon inflations in the culprit coronary artery during the PCI, subsequently producing less chest pain and decrease in ST-segment elevation [12, 13].

Pharmacological preconditioning can be induced by intravenous or intracoronary administration of adenosine or A1 agonists of adenosine [14]. In a recent study performed in rabbits, investigators observed cardioprotective effects of clopidogrel and cangrelor (the intravenous analogue of ticagrelor) that were not attributed to the platelet inhibition but rather to activation of the signal transduction pathways of pre- and postconditioning, involving the reperfusion injury salvage kinases (RISK), including Akt and extracellular-regulated kinase (ERK), as well as adenosine A2B receptors, mitochondrial KATP channels, and redox signaling [15]. This cardioprotective effect of cangrelor was confirmed in a primate animal model as well [16, 17].

#### Improvement of coronary microvascular dysfunction

Coronary microvascular dysfunction has been demonstrated to affect the prognosis of ACS patients. Of note, Furber et al. described that doppler flow velocity parameters in the infarct-related artery are of prognostic value for long-term cardiac events [18]. Additionally, Takahashi et al. found an impaired coronary flow reserve velocity (CFVR) in the infarct-related artery to be significantly associated with increased cardiac event rates at long-term follow-up [19]. Furthermore, a microvascular function has been demonstrated to be altered even in nonischemic regions at distance from the infarcted myocardial tissue [20], and van de Hoef et al. have recently shown that microvascular dysfunction determined in the reference vessel after PCI is associated with a significantly increased long-term cardiac mortality [21].

Microvascular dysfunction is likely to occur also in the setting of non-ST-elevation ACS. In a cohort of 83 non-ST-elevation myocardial infarction (NSTEMI) patients, microvascular obstruction, as assessed by an elevated index of microcirculatory resistance (IMR) that is correlated with microvascular obstruction, was detected by the magnetic resonance imaging and was an independent predictor of adverse cardiovascular outcomes [22]. Marzilli et al. found that in patients with unstable angina, episodes of transient myocardial ischemia at rest are associated with a brisk increase in coronary microvascular resistance and that this increase is prevented by the administration of antiplatelet drugs [23]. Equally important, microvascular dysfunction may also occur following successful PCI; that is, coronary flow reserve has been shown to be impaired in the vascular bed subtended by the treated artery and requires up to 3 months for this microvascular dysfunction to resolve [24]. Finally, coronary microvascular reactivity to adenosine predicted adverse outcomes in women evaluated for suspected ischemia as demonstrated in WISE study [25].

### Pharmacology

#### Mechanism of action (taken from the SmPC of the drug in study)

Ticagrelor, a member of the chemical class cyclopentyl triazolo pyrimidines (CPTP), is an oral, direct-acting, selective, and reversibly binding P_2_Y_12_ receptor antagonist that prevents adenosine diphosphate (ADP)-mediated P_2_Y_12_ dependent platelet activation and aggregation [26]. Ticagrelor does not prevent ADP binding but when bound to the P_2_Y_12_ receptor prevents ADP-induced signal transduction. Since platelets participate in the initiation and/or evolution of thrombotic complications of the atherosclerotic disease, inhibition of platelet function has been shown to reduce the risk of cardiovascular (CV) events such as death, myocardial infarction, or stroke [27].

Ticagrelor also increases local endogenous adenosine levels by inhibiting the equilibrated nucleoside transporter-1 (ENT-1). Ticagrelor has been documented to augment the following adenosine-induced effects in healthy subjects and in patients with ACS: vasodilation (measured by coronary blood flow increases in healthy volunteers and ACS patients), inhibition of platelet function (in human whole blood in vitro), and dyspnea [28, 29]. However, a link between the observed increases in adenosine and clinical outcomes (e.g., morbidity-mortality) has not been clearly elucidated [11, 30].

## Objectives

The main goal of this study is to assess the pleiotropic effects of ticagrelor that could represent possible mechanisms for its beneficial effects on cardiovascular mortality and adverse outcomes.

### Primary objective

Ticagrelor may trigger ischemic preconditioning as compared to clopidogrel in patients with stable multivessel CAD that are undergoing staged PCI.

### Secondary objectives

Ticagrelor may improve microvascular perfusion in the myocardium of patients with stable multivessel CAD that are undergoing staged PCI.

### Study endpoints

#### Primary endpoint

The primary endpoint is the comparison of ticagrelor and clopidogrel for the delta (difference in mm) of the ST-segment elevation, as assessed by the intracoronary ECG during two-step sequential coronary balloon inflation in the index vessel.

#### Secondary endpoints

Secondary endpoints include the following:
Comparison of ticagrelor and clopidogrel on CFR, IMR, and FFR measured in the index vessel at the end of the PCIComparison of ticagrelor and clopidogrel on angina score during coronary balloon inflation

## Materials/Methods

### TAPER-S trial design

This study is a prospective, randomized, blinded, end-point trial that will enroll patients with multivessel CAD requiring scheduled treatment of a second lesion located in a nonculprit vessel. The typical patient will be a patient with purely stable CAD and a scheduled, FFR-guided PCI of any vessel. Patient presenting initially with an ACS, with an intermediate coronary lesion (40–80% in severity, where functional evaluation of the stenosis with FFR must be used based on clinical situation) in a nonculprit coronary artery, for whom a delayed, FFR-guided strategy is chosen, may also be included in the study. In these patients, recovery of the microvascular function requires that at least 1 month has elapsed before re-evaluation of the culprit lesion, as FFR in the acute phase is known to be unreliable [31]. Screening/randomization will take place 1 to 3 days before the index procedure. Randomization will be blocked within each study site, which will allow an even balance of patients to be randomized to either drug at each recruiting center. Patients with FFR > 0.80 (no functionally significant stenosis) will be excluded from the study (Figs. 1 and 2). The study will be conducted in Italy, involving A. Gemelli Polyclinic of the Catholic University of the Sacred Heart in Rome and Grosseto Hospital (Ospedale della Misericordia Grosetto) in Grosetto, Italy.

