**Fig. 2 Fig2:**
[figure not shown]
Flow-chart for patients presenting with stable coronary artery disease

The study is designed to have a total duration of 23 months, with an enrollment period of approximately 20 months. Each patient will be treated with the study drug only during the in-hospital phase, for a minimum of 3 days (Day -1 to Day 1) up to a maximum of 7 days (Day -1 to Day 5). The patient will be hospitalized (as per usual clinical practice) from Day -3 to Day -1 (admission) to Day 0–5 of the study. The total number of enrolled patients will be one hundred (*N* = 100), with a projected 10% drop-out rate and 30% of negative FFR assessment (FFR > 0.80), with a final pool comprising 60 patients who will be evaluated in terms of primary and secondary endpoints. Therefore, the study enrollment will be stopped once one hundred patients are enrolled (Fig. 3).

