### Study drugs

#### Dosing, posology, and route of administration

Ticagrelor will be given in a loading dose of 180 mg (on Day -3 to -1), followed by a dose of 90 mg twice daily (from Day 0 to discharge between Days 1 to Day 5, during the index hospitalization). If the patient is chronically on ticagrelor, the loading dose will be omitted. In case of missed dose, the lapses in therapy should also be avoided. A patient who misses a dose of ticagrelor should take only one tablet (their next dose) at its scheduled time.

Clopidogrel will be given in a loading dose of 600 mg (on Days -3 to -1), followed by a dose of 75 mg once a day (from Day 0 to discharge during Days 1 to Day 5, during the index hospitalization). If the patient is chronically on clopidogrel, the loading dose will be omitted. The antiplatelet switch will be managed according to generally agreed consensus. The details of the Antiplatelet Drug “switch” are specified in the section below.

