#### Antiplatelet drug switch

Patients could be randomized while on treatment to either ticagrelor (previous ACS patients) or clopidogrel (stable patients). For those on long-term ticagrelor or clopidogrel treatment randomized to the corresponding drug, no loading dose will be given, and the patient will be continued on the respective drug. For those randomized to the noncorresponding group, the most recent recommendations regarding antiplatelet drug “switch” will be followed [35, 36] - a loading dose of the other drug will be given, 12–24 h before the scheduled PCI procedure. For patients previously on a long-term ticagrelor treatment, a 24-h washout period (i.e., the withdrawing of a single dose) will be applied before clopidogrel loading dose is initiated, to aid in clearance of the reversible platelet inhibition by ticagrelor and its main metabolite [36]. For both ticagrelor and clopidogrel, the last drug dose will be given at least 4 ± 1 h before the start of the index procedure [37]. After the index procedure, long-term antiplatelet treatment will be administered according to the most recent guidelines [38]. Timing and schedule of all the procedures projected during the protocol visits are detailed in the flow chart table that is available below. See also Additional file 1 for details related to main pharmacological interactions and adverse events definition and reporting.

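### Patients with FFR > 0.80 leave the study after randomisation and dosing; the rule should only make them non-evaluable for the PCI-dependent endpoints

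*Protocol article*

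**What the plan says.** **Order of events.** TAPER-S trial design: "Screening/randomization will take place 1 to 3 days before the index procedure". Dosing, posology, and route of administration: "Ticagrelor will be given in a loading dose of 180 mg (on Day -3 to -1") and "Clopidogrel will be given in a loading dose of 600 mg (on Days -3 to -1"). Patients already on the assigned drug skip the loading dose but continue that drug. Antiplatelet drug switch: "the last drug dose will be given at least 4 ± 1 h before the start of the index procedure".

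**Exclusion.** TAPER-S trial design states that patients with FFR > 0.80 ("no functionally significant stenosis) will be excluded from the study". The numbers paragraph of that section projects 10% drop-out and 30% negative FFR among 100 enrolled, "with a final pool comprising 60 patients who will be evaluated in terms of primary and secondary endpoints". Sample size says the 100 allow for patients who turn out not to need PCI once FFR is known.

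**FFR as an outcome.** Secondary endpoints lists: "Comparison of ticagrelor and clopidogrel on CFR, IMR, and FFR measured in the index vessel at the end of the" PCI. The abstract's Methods describes changes in CFR, IMR and "FFR measured in the culprit vessel and reference vessel at the end of PCI".

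**Data that do not depend on PCI.** Table 1 schedules dyspnoea, VASP/VerifyNow and adverse events from Visit 0 onwards. Assessment of platelet reactivity takes samples after randomisation and just before the procedure, and uses the left-overs for adenosine and ENT-1. Sample size mentions a co-primary safety endpoint, analysed by Fisher's exact test.

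**The concern.** Membership of the analysed set is decided after treatment has begun, by a reading that treatment could shift. The Rationale says ticagrelor moves the adenosine flow-response curve to the left, and hyperaemia in this trial is induced with intravenous adenosine. If ticagrelor changes FFR, the two arms pass the 0.80 threshold at different rates and the retained patients differ in lesion severity. The 50 + 50 envelopes balance those randomised, not those retained.

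Separately, the exclusion covers the whole study. Followed literally, it removes about 30 treated patients from comparisons that need no balloon inflation and no PCI, including safety.

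A related inconsistency concerns the microvascular endpoint. The abstract has a change in two vessels; Secondary endpoints has one vessel, at the end of PCI.

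**Working it through.** **1. The plan's own figure.** 100 × (1 − 0.30 − 0.10) = 60, which matches. Applied in sequence, 100 × 0.70 × 0.90 = 63, which does not. FFR exclusions number 30, or 100 × 0.90 × 0.30 = 27 if drop-out comes first. The FFR-negative patients are therefore among the 100 randomised.

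**2. Which endpoints need PCI.**

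| Measure | Obtainable if FFR > 0.80 and no PCI? |
|---|---|
| ST delta, angina score | No: need balloon inflation |
| CFR, IMR, FFR at end of PCI | No: no end-of-PCI value exists |
| Adverse events, safety endpoint | Yes, as far as the text shows; the safety endpoint is not defined in the article |
| Dyspnoea | Yes |
| VASP, VerifyNow, adenosine, ENT-1 | Yes: sampled before the procedure |

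**3. How far a drug effect on FFR could change entry (assumptions, not protocol figures).** Take FFR as normal with SD 0.08 to 0.10 and 30% above 0.80 on clopidogrel, so the standardised cut is c = 0.524. If ticagrelor lowers FFR by d, its negative rate is 1 − Φ(0.524 + d/SD).

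| d | FFR-negative on ticagrelor | Extra ticagrelor patients retained, of 50 |
|---|---|---|
| 0.01 | 26–27% | 1.7–2.1 |
| 0.02 | 22–23% | 3.3–4.0 |
| 0.03 | 18–20% | 4.8–5.8 |

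**4. Resulting bias on ST.** Assume no true effect on ST, SD 5 mm (the upper value under Sample size) and correlation ρ = 0.3 to 0.5 between FFR and ST delta. The mean standardised FFR of retained patients is −φ(c)/Φ(c), and bias = ρ × SD × the between-arm difference in that mean.

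- Clopidogrel, 30% negative: mean −0.497.
- Ticagrelor, 20% negative (c = 0.842): mean −0.350, difference 0.147. Bias = 0.3 × 5 × 0.147 = 0.22 mm to 0.5 × 5 × 0.147 = 0.37 mm. A 40% negative rate gives the same size with the opposite sign.
- With d = 0.02 from step 3: 0.14 to 0.30 mm.
- With no drug effect on FFR: zero.

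With 30 per arm the standard error is 5 × √(2/30) = 1.29 mm. A bias of 0.22 to 0.37 mm raises a two-sided 5% type I error to about 5.3–5.9%.

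**5. What the wider exclusion could cost.** Assume the dyspnoea rates cited in the Rationale from a study in stable disease, 38.6% on ticagrelor and 9.3% on clopidogrel, carry over. Exact power of Fisher's test (two-sided 5%):

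| Patients per arm | Power |
|---|---|
| 30 (the evaluable pool) | 69% |
| 45 (all but the 10% drop-outs) | 88% |
| 50 (all randomised) | 92% |

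**The case against.** **PCI-dependent endpoints.** ST delta and angina score exist only where a balloon is inflated, and the listed CFR, IMR and FFR endpoints are taken at the end of PCI. This stands in full. A reader might infer that the microvascular endpoints lose a third of their data, so that analysing 90 rather than 60 would shrink their standard error. The text does not support that: FFR-negative patients have no end-of-PCI value to supply.

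**Size of the bias.** A reader might infer that the 60 are no longer a randomised comparison at all. That goes too far. Bias needs both a drug effect on FFR and a link between FFR and ST delta, and the protocol quantifies neither. A left-shifted dose-response curve need not alter the response at the steady-state maximal hyperaemia that the protocol aims for, so the bias may be nil. This is also a declared exploratory pilot. The blinding of PCI operators protects judgement, but not against a drug effect on the reading.

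**Safety data.** The sentence on 60 patients mentions only primary and secondary endpoints. Statistical analysis describes all variables by arm and visit and leaves the populations to the SAP, and adverse-event detail sits in an additional file; neither is shown. It is therefore not established that safety data will be discarded. What remains is that the one stated rule removes these patients from the study, and no sentence in the article keeps them in any analysis.

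**Timing.** The flow charts are not shown. That FFR follows dosing is inferred from the visit schedule and from the Sample size text, and that the gating FFR uses the adenosine infusion described for CFR and IMR is also an inference. The first is well supported; the second is likely.

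**Conclusion.** The point holds as a should-fix matter of wording and analysis sets. About 30 of 100 randomised and treated patients are removed by a Day 0 measurement that the protocol itself treats as a possible drug outcome. For the primary endpoint the restriction cannot be avoided. Its likely effect is a few tenths of a millimetre against 4 mm, under assumed correlations of 0.3 to 0.5 and an assumed difference in FFR-negative rates, and zero if the drug leaves FFR unchanged. The primary result should nevertheless be presented as conditional on FFR ≤ 0.80.

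The more tangible problem is that the exclusion is wider than it needs to be. If applied literally, power for a dyspnoea difference of the cited size would be 69% instead of 88 to 92%. That figure is only an illustration: dyspnoea is not a listed endpoint, and the cited rates may not apply to an exposure of 3 to 7 days.

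The mismatch between the abstract and Secondary endpoints, on the vessel or vessels and on change versus end-of-PCI value, is a plain inconsistency.

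**What to change.** 1. In TAPER-S trial design, replace exclusion from the study with: *not evaluable for the PCI-dependent endpoints (ST delta, angina score, end-of-PCI CFR, IMR and FFR)*.
2. Keep every randomised and dosed patient in the adverse-event, safety-endpoint, dyspnoea, platelet-reactivity and adenosine/ENT-1 analyses.
3. Report pre-PCI FFR and the proportion > 0.80 by arm among all patients assessed, as a check on selection.
4. Describe the primary analysis as conditional on FFR ≤ 0.80.
5. Make the abstract and Secondary endpoints agree on the vessel or vessels and on whether the microvascular endpoint is a change or an end-of-PCI value.

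The cost is wording, analysis sets and one descriptive table; the gating FFR is measured anyway. The safety set will differ from the efficacy set, and FFR-negative patients may have shorter drug exposure, so exposure should be shown alongside.

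Adding a pre-PCI CFR/IMR measurement for this purpose is not recommended. It means extra injections and possibly more intravenous adenosine before the inflations, and the section on activation of preconditioning says intravenous adenosine can itself induce preconditioning.
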